### Outcome measures

The evaluations will take place at three time - points: prior to treatment (week 0), post-treatment (week 6), and three months subsequent (week 12). The primary outcomes will entail the measurement of diaphragm excursion using ultrasound
^
50
^ and chest expansion (CE) using a tape measure.
^
51
^ Secondary outcomes will also be employed: maximal inspiratory and expiratory pressures (MIP/MEP),
^
52
^
^,^
^
53
^ dysfunctional breathing (Nijmegen questionnaire – - NQ),
^
54
^ asthma Control (ACT),
^
55
^
^,^
^
56
^ quality of life (SF-12v2),
^
57
^ and dyspnea (Borg scale).
^
58
^
Table 2. illustrates the SPIRIT
^
34
^ schematic protocol of the study along with the schedule of assessments.

**Table 2. T2:** Standard protocol items: recommendations for interventional trials of this study (SPIRIT).

TIME POINT	Enrollment (-T1)	Allocation (T0)	Pre-intervention (T1)	Intervention	Post-Intervention	
					(T2)	(T3)
ENROLLMENT:						
Eligibility screen	X					
Informed consent	X					
Demographic information	X					
Allocation		X				
Intervention						
MDRT + BRE						
BRE						
ASSESMENTS						
Neurological and cardiovascular assessments	X					
Primary outcomes: US			X		X	X
CE			X		X	X
Secondary outcomes: MIP/MEP			X		X	X
NQ			X		X	X
ACT			X		X	X
Borg scale			X		X	X
SF-12v2			X		X	X

-T1: one month before first treatment; T0: one week before first treatment (week 0); T1: 20 minutes before first treatment; T2: after the last treatment, (week 6); T3: follow-up 6 weeks from the last treatment (week 12).

**
*Primary outcome measures*
**

**Diaphragmatic excursion assessment with ultrasonography:** Numerous studies have confirmed the effectiveness of the US to evaluate diaphragmatic function. Since 1970,
^
59
^ the US has been utilized to assess the diaphragm’s mobility. Modern medicine accepts its use as a completely safe method. The diagnostic US has 93% sensitivity and 100% specificity.
^
17
^ The examiners are not exposed to any radiation, and there is no need for special preparation, allowing for as many safe applications as required. The US offers the option of a dynamic inspection of the affected area in real time. The diaphragmatic excursion is measured in cm/mm. In this study the excursion of the diaphragm will be measured using the ultrasound device, E-CUBE 8LE (Seoul, Republic of Korea).

**Chest wall expansion (CWE):** In clinical and research practice, the inch tape measure is an alternative method for assessing chest expansion.
^
60
^ By placing the tape measure at the level of the axilla (about the level of the sternal angle of Louis), the level of the xiphoid process, or between the xiphoid process and the umbilicus, the therapist identifies the upper, middle, and lower chest wall expansion, respectively. The therapist should repeat the measurement at least three times for each level for higher fidelity.
^
51
^ A tape measure (in centimeters) will assess the variance between values recorded during deep inhalation and exhalation, with greater values signifying improved results.
^
51
^ Norms have been developed according to age and sex.
^
60
^

**
*Secondary outcome measures*
**

**Nijmegen Questionnaire (NQ):** The Nijmegen Questionnaire is a reliable and valid tool for assessing dysfunctional breathing
^
62
^ in clinical practice and research. It is designed to identify the Hyperventilation Syndrome (HS). A score greater than 23 indicates the presence of HS in the general population. The NQ has shown 91% sensitivity and 95% specificity.
^
61
^
^,^
^
62
^ In previous research, NQ scores of 20, 22 and 23 have been used as cut-off scores to detect HS in subjects with and without asthma.
^
63
^
^–^
^
65
^ The NQ questionnaire has been validated in Greek adults with asthma, providing evidence of validity and reliability of measurements with a cut-off score of >17.
^
66
^

**Asthma control test (ACT):** The ACT questionnaire is a valid and reliable clinical and research tool.
^
67
^ Its quick completion time is one of its key features. It has five items, all about the most recent four weeks.
^
68
^
^,^
^
69
^ The ACT evaluates the frequency of wheezing and other general asthma symptoms and the need for emergency control self-assessment. The score ranges from 5 (poor control of asthma) to 25 (good control of asthma). An ACT score >19 indicates controlled asthma. The ACT has been validated in the Greek population with asthma and has shown high indices of internal consistency (0.72) and test–retest reliability (IR = 0.85).
^
59
^

**Sf-12v2 questionnaire:** A simplified version of the SF-36 includes medications, and how well asthma affects daily functioning and overall asthma. The SF-12v2 is a practical, reliable, and valid way to assess physical and mental health. With one or two questions per domain, it assesses the exact eight health dimensions as the SF-36v2, which includes Physical Functioning, Role-Physical, Bodily Pain, General Health, Vitality, Social Functioning, Role-Emotional, and Mental Health. The SF-12 is a valid alternative to the lengthy SF-36 for the self-assessment of quality of life by assessing the health status of healthy and patient population groups.
^
69
^ Higher ratings indicate better physical and mental wellbeing, ranging from 0 to 100.
^
70
^ It has been suggested that a cut-off of 50 or less can be used to identify a physical condition, while a score of 42 or less may signify clinical depression.
^
70
^ The Sf-12v2 has been weighted in the Greek general population.
^
71
^

**Borg scale:** The Borg dyspnea scale is a simple, non-proprietary scoring system. It is extensively used in clinical and research practice to evaluate symptoms of shortness of breath and provides valuable data.
^
72
^
^,^
^
73
^ It begins with 0 (no dyspnea), and goes up to 10 (extreme dyspnea). As a result, healthcare professionals must give patients enough time to learn and ensure they comprehend it before using it.
^
74
^

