### Statistical analysis

The investigation will employ IBM SPSS software, specifically version 28, as the primary analytical tool for comprehensive data processing. Descriptive statistics will be employed to elucidate the distributional characteristics of the dataset. Subsequently, the Shapiro-Wilk test will be utilized to assess data normality for each dependent variable (including US, CWE, ACT, NQ, SF-12v2, and Borg scale) independently. Should normality assumptions be met, parametric tests, specifically the 2×3 ANOVA repeated measures, will be employed, accompanied by Bonferroni adjustment, to investigate the interaction between intervention (experimental and control groups) and time points (0, 6, and 12 weeks). Moreover, to evaluate the homogeneity of variance, Levene’s test will be conducted. The predetermined level of statistical significance is set at p<0.05.

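### Two primary outcomes share one 0.05 level with no stated rule for combining them; if either may carry the claim, the false-positive rate is about 8 to 10%

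*Protocol article*

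**What the plan says.** Under Outcome measures, the protocol article makes two variables primary: "The primary outcomes will entail the measurement of diaphragm excursion using ultrasound", together with "chest expansion (CE) using a tape measure". The Abstract and Table 2 agree. Table 2 schedules both before treatment, after the last treatment (week 6) and at follow-up (week 12).

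The description of chest wall expansion covers three tape positions, from which "the therapist identifies the upper, middle, and lower chest wall expansion, respectively". It adds: "The therapist should repeat the measurement at least three times for each level for higher fidelity". No level is chosen and no combined value is defined. However, Table 2 has a single CE row and the Statistical analysis section lists a single CWE variable.

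The Statistical analysis section plans a 2×3 repeated-measures ANOVA, "accompanied by Bonferroni adjustment, to investigate the interaction between intervention (experimental and control groups) and time points". It then gives one threshold: "The predetermined level of statistical significance is set at p<0.05". The Sample size calculation section uses another: alpha 0.01, two-tailed, with d = 1.86, power 0.85 and 15% attrition, giving 24 people. It does not name the outcome to which d = 1.86 belongs and does not link the 0.01 to multiplicity.

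**The concern.** With two primary outcomes, the error rate of the trial's main claim depends on how the two results are combined. If both must be significant, testing each at 0.05 is safe. If either is enough, it is not, unless the level is shared or the tests are ordered. The article fixes the number of primary outcomes and the test level, but not the rule that connects them.

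The Bonferroni adjustment does not close the gap as worded. It is attached to a model whose factors are group and time, with no outcome factor, so the natural reading is an adjustment within one outcome.

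At stake are the credibility of a positive result and its meaning. A reader could not tell which outcome, which chest value or which week decides the trial. The two alpha levels add to the problem: a trial sized at 0.01 but analysed at 0.05 gives up protection that its own sample size had already paid for.

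**Working it through.** **1. The plan's own sample size.** Inputs from Sample size calculation: two-sided alpha 0.01, power 0.85, d = 1.86, 15% attrition. For a two-sample t-test with n per arm, the noncentrality is d√(n/2) on 2n − 2 degrees of freedom.

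- n = 9: power 0.830, too low.
- n = 10: noncentrality 1.86 × √5 = 4.159, critical value 2.878, power 0.883.
- Attrition: 20 / 0.85 = 23.5, rounded up to 24.

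The stated 24 is reproduced, at 0.01.

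**2. Two primary outcomes, each at 0.05, either sufficient.** With no true effect and independent tests, 1 − 0.95² = 0.0975. The documents give no correlation between the outcomes, so a range is assumed (bivariate normal test statistics):

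| Correlation | At least one false positive |
|---|---|
| 0 | 9.75% |
| 0.3 | 9.5% |
| 0.5 | 9.1% |
| 0.7 | 8.4% |

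A simulation of the planned group-by-time F test (10 per arm; correlation between time points assumed to be 0.6) gives 5.1% for one outcome and 8.5 to 9.6% for two, over correlations between outcomes of 0.7 to 0.

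**3. If the three chest levels were also tested separately.** That makes four tests: 1 − 0.95⁴ = 18.5% if independent, and 17.4%, 15.6% and 13.0% at correlations of 0.3, 0.5 and 0.7. This applies only under an analysis that the article does not specify.

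**4. Time points.** The interaction test is one omnibus test per outcome, so weeks 6 and 12 add almost nothing to the error rate (5.1% in step 2). If the two weeks were instead compared separately, two outcomes would give 14.3 to 17.0% unadjusted, and 7.6 to 9.0% with Bonferroni over the two weeks only. The excess that remains comes from having two outcomes.

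**5. What control achieves.**

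- 0.025 per outcome: 1 − 0.975² = 4.9% if independent, lower if positively correlated.
- 0.01 per outcome: 1 − 0.99² = 1.99%.
- Both required at 0.05: with no effect on either outcome, the chance that both are significant cannot exceed 5%.

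**6. Power with 10 evaluable per arm** (same t-test formula; the d values below 1.86 are assumptions):

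| d | 0.05 | 0.025 | 0.01 |
|---|---|---|---|
| 1.86 | 97.5% | 94.7% | 88.3% |
| 1.2 | 72% | 60% | 45% |
| 1.0 | 56% | 44% | 29% |

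These are t-test powers, as in the plan's own calculation, not powers for the 2×3 interaction.

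**The case against.** The strongest reply is that a success rule, a testing order and a deciding time point are often left to an analysis plan, and none is shown here. For those items taken alone, that is fair. It does not dispose of the point, because the article itself labels two outcomes primary, sets one level of 0.05 and words its only adjustment for something else. It also states two different alphas.

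A second reply is that the scope of the Bonferroni adjustment is not defined. If it was meant across outcomes, the family error would be at or below 5%. That is possible, but the text does not say it, and one sentence would settle it.

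A third is that the 8 to 10% assumes that either outcome suffices, a rule the article does not state. This stands: the figure is conditional.

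Some stronger readings are tempting but unsupported:

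- A reader might take 18.5% as the error rate. The three levels appear in a general description of the tape method, while Table 2 and the analysis section each list one chest variable.
- A reader might count weeks 6 and 12 as further chances of a false positive. Under one interaction test per outcome they add little; what they leave open is which effect decides.
- A reader might cite the word independently in the analysis section as proof of separate efficacy tests. There it describes the normality checks. Separate tests follow instead from the 2×3 model having no outcome factor.

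**Conclusion.** The concern holds in a bounded form. Two primary outcomes share one 0.05 level, the stated adjustment is not said to cover them, and no rule says whether one or both must be positive. If either may carry the claim, the family false-positive rate is 9.75% under independence and about 8.4 to 9.5% at assumed correlations of 0.7 to 0.3, nearly double the nominal level. The 13 to 18.5% range depends on testing the chest levels separately and should not be presented as a property of the plan.

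The contradiction between 0.01 for sizing and 0.05 for testing needs no assumption. Used as the test level for each of the two outcomes, 0.01 would hold the family error at about 2%.

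It would be wrong to infer that correction is free. That holds only if d = 1.86 applies to the outcome concerned, and the article does not say which outcome it describes. Nor do the documents rank excursion above chest expansion, or week 6 above week 12, so the choice of what comes first belongs to the sponsor.

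**What to change.** Before the data are analysed, state one of these rules for excursion and chest expansion:

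- Holm, or Bonferroni at 0.025 each, if either may support a positive claim.
- Each tested at the 0.01 used for the sample size, which also reconciles the two alphas.
- Both required to be significant at 0.05.
- One named as the single primary, with the other tested only if the first succeeds.

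Whichever is chosen, define chest expansion as one pre-named level or one combined value, name the deciding time point, say what the Bonferroni adjustment covers, and give the same alpha in the sample size and analysis sections, or explain the difference.

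The change is to wording and needs no more participants if d = 1.86 holds for each outcome. The cost is power per outcome. Moving from 0.05 to 0.025 with 10 evaluable per arm takes it from 97.5% to 94.7% at d = 1.86, but from 56% to 44% at d = 1.0. Requiring both outcomes costs power through the weaker one, and a fixed sequence means that the second outcome cannot support a claim alone.

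On timing, Data management sends the spreadsheet to the statistician only on completion, so the rule can precede the analysis. The Protocol amendments section says that no further modifications could be made, whereas Research ethics approval provides for disclosing modifications to the Ethics Committee. The sponsor should resolve which applies and record the rule with its date.

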### Randomization and blinding procedures

Following the initial assessment, eligible volunteers will be randomly assigned to two experimental groups if they meet the inclusion criteria by the secretariat of the Pulmonology Department of the GCHAA. The randomization will be carried out using sealed envelopes. Individuals will have their allocation concealed through the use of sealed envelopes that are sequentially numbered and opaque.
^
36
^ The envelopes will be opened only by the primary researcher, who is responsible for the research project and coordination of the study. The pulmonologist who will perform lung function testing on all participants (well-maintained and regularly calibrated equipment), diagnose asthma and perform the measure of chest expansion, the radiologist who will perform the ultrasonography (US), and the two separate physical therapists, who will implement the DMRT and BRE will be unaware of the group allocation.

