### Initial assessments

A pulmonologist of GOHK with years of experience diagnosing and treating asthma patients will examine the chest expansion, the pulmonary function, and diagnosis of asthma. The radiologist will perform the US assessment, and the secretariat of the GOHK will administer the questionnaires in a random order and collect all data.

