**Interventions**

The pulmonologist and the main researcher of the protocol will organize two online sessions with all the participants after the randomization. In one session, participants will be informed by the pulmonologist about (a) general asthma information, (b) asthma triggers, (c) recognition of asthma symptoms, (d) medication and proper use of asthma medications (inhaler techniques), (e) smoking, and (f) asthma control (symptom control/future risk domains/long-term goals).
^
38
^ As for the last domain (asthma control), information will be provided regarding, (i) the dynamic changes of asthma, (ii) the recognition of these changes based on PEF values and symptoms, (iii) the importance of early detection of clinical signs of worsening and the immediate initiation of appropriate medication.

At the second online session the participants will be informed by the main researcher about (a) the breathing pattern, (b) the pathological pattern of breathing that is developing both in stable phase and in paroxysm,
^
39
^ (c) the role of physiotherapy and specifically about the BRE in PR, (d) the formation of a trusting relationship between a person living with asthma and a medical professional (e) the importance of self-efficacy in asthma self-management
^
40
^
^–^
^
43
^ and (f) the self-efficacy enhancement process.

Following the two online sessions, there will be a discussion between patients and health professionals (pulmonologist - main researcher) lasting approximately one hour, during which patients can share their objectives, values, apprehensions, support and commendations. The structure of the online session will be determined by a) the long-term objectives for asthma management
^
5
^ and b) the health belief model.
^
44
^
^,^
^
45
^ Regarding the treatment sessions, every participant will receive twelve sessions twice weekly for six weeks, lasting one hour per session. Individual sessions will be provided in patients’ homes under the same conditions (
*e.g.*, day, time of day, temperature, therapeutic bed, and patient’s position).

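### Table 2 takes baseline outcomes about a week after allocation, whereas the text takes them before randomisation; the two must be reconciled

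*Protocol article*

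**What the plan says.** The protocol article gives the order of baseline and allocation in two ways.

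- **Table 2 (Outcome measures).** Allocation is marked in the T0 column. Ultrasound, chest expansion, MIP/MEP, NQ, ACT, Borg and SF-12v2 are first marked in the T1 column, and none is marked earlier. The footnote defines the columns: "T0: one week before first treatment (week 0); T1: 20 minutes before first treatment".
- **Randomization and blinding procedures.** Here the order is the reverse: "Following the initial assessment, eligible volunteers will be randomly assigned". Assessment comes first, then randomisation, and the secretariat is named as carrying it out.
- **Initial assessments.** The pulmonologist "will examine the chest expansion, the pulmonary function, and diagnosis of asthma". Then: "The radiologist will perform the US assessment, and the secretariat of the GOHK will administer the questionnaires in a random order". The initial assessment therefore includes both primary outcomes and the questionnaires.

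Two further statements bear on who may know the allocation. "The envelopes will be opened only by the primary researcher", and the same section lists the pulmonologist, the radiologist and the two therapists as unaware of it. Participants, the secretariat and the main researcher are not on that list. Under Data collection methods, the main researcher collects the outcome data before and after the intervention.

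**The concern.** A baseline is protected by randomisation only if it is measured before anyone can act on the allocation. Under the order in the text, a between-arm difference at week 0 can arise only by chance. Under the order in Table 2, it can also arise because someone knows the arm: a participant who expects hands-on treatment may answer a questionnaire differently or put different effort into a breathing manoeuvre, and a person who handles both allocation and data collection may influence either.

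This matters because week 0 is one of the three time levels in the planned 2×3 repeated-measures ANOVA, whose target is the group-by-time interaction. A difference created at week 0 would be read as a difference in change. The Table 2 order also leaves a gap of about a week in which a randomised participant can withdraw before any outcome has been measured.

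**Working it through.** The protocol states no figure on this point to reproduce. The check is a comparison of sequences, followed by a short piece of algebra.

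**1. The gap under Table 2.** Take the first treatment as time zero. Allocation (T0) is at −7 days, and baseline (T1) is at −20 minutes. The gap is 7 × 24 × 60 − 20 = 10,060 minutes, and 10,060 / 1,440 = 6.99 days, with allocation first.

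**2. The two orders side by side.**

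| Source | First | Second |
|---|---|---|
| Randomization and blinding procedures; Initial assessments | Chest expansion, ultrasound, questionnaires | Randomisation |
| Table 2 and its footnote | Allocation (T0) | All outcomes (T1) |

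Both could be true only if outcomes were measured twice before treatment. Table 2 shows one pre-treatment measurement, and the Outcome measures text names three evaluations in all, at weeks 0, 6 and 12. The text is less complete on one item: Initial assessments does not name MIP/MEP, so for that outcome only Table 2 gives a position.

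**3. Who could carry knowledge of allocation into T1.**

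- *Participants*: not listed as unaware. NQ, ACT, SF-12v2 and Borg are their own reports. MIP/MEP, and chest expansion between full inspiration and expiration, depend on their effort.
- *Secretariat*: named in assigning participants and in giving the questionnaires; not listed as unaware.
- *Main researcher*: collects outcome data; not listed as unaware. The person who opens the envelopes is called the primary researcher. The two titles probably mean one person, but that is an assumption.
- *Pulmonologist and radiologist*: stated to be unaware. They measure chest expansion and ultrasound.

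**4. How a baseline shift reaches the test.** Write M(g,t) for the mean of group g at week t, with E for the experimental and C for the control group. The interaction is built from contrasts such as

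D(6) = [M(E,6) − M(E,0)] − [M(C,6) − M(C,0)], and likewise D(12).

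If knowledge of allocation moves the week 0 means by b(E) and b(C) and leaves later means alone, D(6) and D(12) each change by −[b(E) − b(C)]. The contrast between weeks 12 and 6 does not change. If both arms move equally, b(E) − b(C) = 0 and nothing happens. Only a difference between arms does harm, and it then passes in full into the two contrasts that use baseline.

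**5. Withdrawal between T0 and T1.** With 12 per arm, one such participant is 1/12 = 8.3% of an arm, with no outcome value at all.

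**The case against.** The strongest reply is that this is a documentation slip. The text already gives the right order, and the two primary outcomes are measured by people stated to be unaware of allocation. Nothing says that participants learn their arm before T1. These points limit the concern. They make assessor bias on ultrasound and chest expansion unlikely under either order, and they make influence through participants a possibility only. They do not settle which order is followed, and they do not cover self-report or participant effort.

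A second defence is that the initial assessment is only an eligibility screen. That is weak, because the section under that name lists both primary outcomes and the questionnaires.

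Several stronger readings are tempting but unsupported:

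- *Baseline is contaminated by the education sessions.* The article says the pulmonologist and main researcher "will organize two online sessions with all the participants after the randomization", but it gives no date relative to T1, and Table 2 does not list the sessions. That they precede baseline is a likely inference. They go to both arms, so by themselves they would not create a between-arm difference.
- *Every outcome is affected.* The stated unawareness of the two primary-outcome assessors speaks against so general a claim.
- *A false-positive rate can be attached.* That needs the size of the shift and the correlation between baseline and follow-up. The documents give neither. A comparison of follow-up values alone would not be biased by a baseline shift at all.
- *The assessments cannot fit into 20 minutes.* The footnote gives a time point, not a duration, and no assessment times are stated.

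On practicality, the trial was due to run from January 2023 to January 2024, the protocol version is dated 29/09/2023, and Protocol amendments says no further modification could be made. For most participants the order may already be fixed in practice, so much of the remedy lies in reporting.

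**Conclusion.** The contradiction is certain: Table 2 puts baseline about seven days after allocation, the text puts it before randomisation, and no other section resolves the conflict. The consequence is conditional. If Table 2 describes practice, a route exists by which knowledge of allocation could shift self-reported outcomes (NQ, ACT, SF-12v2, Borg) and effort-dependent ones (MIP/MEP, chest expansion), and any between-arm shift would enter the interaction test. This assumes that at least one of the participants, the secretariat or the main researcher knows the allocation by T1, which the documents neither state nor exclude. The direction and size of any bias cannot be derived. If the text describes practice, there is no bias from this source and only the table is wrong. The point is worth correcting because a reader cannot at present tell which case applies.

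**What to change.** Correct Table 2 and its footnote so that all primary and secondary baseline measurements, MIP/MEP included, are completed before the allocation envelope is opened. This agrees with the randomisation and initial-assessment sections. It needs no new procedure and no change to the education sessions. The cost is a few more days between baseline and first session.

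For participants already enrolled, record for each whether baseline preceded allocation, and report it. If the Table 2 order was followed, correct the text instead, disclose the order as a limitation, and report anyone randomised who left before T1. The cost is one dated entry per participant, at most 24 at the planned sample size. Because the article says that the protocol is closed to modification, the correction should be notified to the ethics committee as the resolution of an internal inconsistency.
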